## Abstract

**Background:**

Avoidant/restrictive food intake disorder (ARFID) is an eating disorder prevalent in children and associated with several health and psychosocial impairments. Despite its prevalence, limited treatment services are available and children with ARFID often do not receive specialized care. Cognitive-behavioral therapy has shown feasibility in face-to-face trials supporting proof-of-concept. Digital interventions could increase treatment accessibility in this population.

**Methods:**

In a single-armed intervention trial (*N* = 40) children aged 8–14 years with a primary diagnosis of ARFID and their caregivers will receive a digital cognitive-behavioral therapy. The intervention consists of a 12-session program, combining video therapy sessions with children and caregivers and self-guided modules. Assessments occur at baseline, mid-treatment, post-treatment, and 4-week follow-up with additional symptom monitoring questionnaires per session. Primary outcomes include feasibility, recruitment and retention rate. Secondary outcomes include ARFID symptoms (e.g., Eating Disorder Examination ARFID module, Nine Item Avoidant/Restrictive Food Intake Disorder screen), food neophobia (Food Neophobia Scale) and quality of life (Generic Quality of Life Instrument for Children-Revised).

**Discussion:**

This study evaluates the feasibility and proof of concept of a therapist-guided digital intervention for ARFID. If feasible and acceptable, the digital intervention may help to increase treatment access for children with ARFID in German-speaking countries. Furthermore, findings can inform future larger-scale randomized control trials and the development of digital interventions for ARFID.

**Clinical Trial Registration:**

https://drks.de/search/de/trial/DRKS00038026/details, identifier DRKS00038026.

## Introduction

1

Avoidant/restrictive food intake disorder is a feeding and eating disorder associated with several negative health consequences (e.g., nutritional deficiencies and low bone health) (1). According to the *Diagnostic and Statistical Manual of Mental Disorders Fifth Edition* (*DSM–5*) (2) the diagnostic criteria include significant weight loss or failure to achieve expected growth, nutritional deficiencies, dependence on enteral feeding or nutritional supplements, and/or marked impairment in psychosocial functioning. ARFID is most common in children and early adolescents with prevalence ranging from 0.3% to 15.5% in community and school samples and from 5% to 22.5% in pediatric eating disorder services (3). The onset is younger compared to other restrictive eating disorders such as anorexia nervosa (3). ARFID is heterogeneous with variable presentations (sensory sensitivity, lack of interest in eating or food, or fear of negative consequences of eating) (2). Studies have shown that 61-77% of children and adolescents with ARFID present with sensory sensitivity as at least one of their presentations (4–6). Despite its prevalence in childhood and associated health consequences, the majority of individuals with eating disorders, including ARFID, do not receive specialized treatment services (7, 8).

Various interventions have been developed to treat ARFID in children and adolescents. While fully powered randomized control trials are currently lacking, pilot studies suggest that outpatient therapies that involve families demonstrate feasibility and acceptability for pediatric patients (9–12). In a pilot study, a technology-supported behavioral day treatment program for young children aged 1–6 years increased the number of bites accepted by the children from pre- to post-intervention (9). For slightly older children, aged 6–14 years, Shimshoni, Silverman (10) developed the ARFID Supportive Parenting for Anxious Childhood Emotions (SPACE) to target parental accommodation to the child’s eating behavior. Pilot study results revealed high satisfaction and a reduction in ARFID symptoms following treatment (10). Furthermore, family-based treatment adapted for ARFID (FBT-ARFID) of children aged 5 to 12 years showed promising results in a feasibility randomized control trial. The findings showed that families accepted FBT-ARFID and demonstrated medium to large effect size differences for clinical severity supported FBT compared to treatment as usual (11).

Cognitive behavioral therapy interventions have also shown promise for treating ARFID. A clinical case series of children ages 10–18 years with ARFID who received CBT for ARFID delivered in a day treatment setting demonstrated that 10 out of 11 children were in remission at three-month follow-up (13). Furthermore, Thomas & Eddy (2019) developed an outpatient manualized Cognitive-Behavioral Therapy for Avoidant/restrictive food intake disorder (CBT-AR (14)) that they and others have now tested in two open trials (12, 15) and several case studies (16–18). CBT-AR was developed for children, adolescents and adults from the age of 10 years and leverages food exposure as the key intervention. It is delivered in an individual or family supported format, with the latter being recommended for children and adolescents under the age of 16 or older adolescents who are underweight (14). Two studies showed that CBT-AR is feasible as well as acceptable in both pediatric (15) and adult (12) patients, demonstrating evidence for proof of concept (12, 15). In the pediatric sample, 70% achieved remission at post treatment and patients incorporated an average of 16.7 new foods in their diet (15). Moreover, CBT-AR suggests different exposure-based treatment strategies tailored to the three different presentations of ARFID (sensory sensitivity, lack of interest in eating or food or fear of negative consequences), making it flexible to adapt to patient specific presentations. Importantly, patients with sensory sensitivity showed significantly greater improvement when receiving the targeted intervention for this presentations compared to those who did not receive the presentation-specific intervention in a CBT-AR intervention study (19). To our knowledge, none of the previous cited interventions have been evaluated in German speaking countries where ARFID prevalence has been established (4, 20, 21), and specialized treatment services are currently lacking.

Although these novel treatments for ARFID are under study and increasingly utilized in the community, most individuals with ARFID in the community struggle to access these evidence-based approaches. Indeed, individuals with ARFID face various health care barriers and report long health care journeys before reaching specialized health care services (22–25). This delay may be attributed to health care professionals and clinicians reporting difficulties in identifying ARFID and the lack of clear treatment recommendations. This highlights the need for more intervention to identify accessible evidence based treatments (24, 26). Furthermore, an interview-based life history study of families’ experiences in the healthcare system revealed that shame experienced by parents and perceived blaming by healthcare providers might hinder treatment access (23). Additionally, the lack of specialized treatment options in non-urban areas (23) and family time constraints may further decrease accessibility (27).

One potential solution to increase accessibility and flexibility of treatment are digital health intervention (i.e., use of technology to support health) (7, 28). According to the World Health Organization digital intervention describes the use of digital technologies to enhance health fields, including ehealth (i.e. the use information and communications technology in health) or other technology such as artificial intelligence (7). Digital health interventions can provide a more private treatment access than standard face to face therapy, thereby reducing shame as a treatment barrier (29). Moreover, they have been shown to be feasible and effective for children and adolescents with eating disorders (30). Many of the ARFID therapies have been successfully delivered via video therapy in the previously mentioned trials (10, 16, 27, 31). Beyond video therapy, digital ehealth interventions also include web-based delivery of information in interactive modules or apps. These self-guided or asynchronous therapist-guided modules allow for flexible and individualized timing of the intervention without relying on availability of a study therapist. In a non-clinical population, nutritional interventions delivered to parents have been shown to improve nutritional intake (e.g. fruit and vegetable consumption) in children (32). However, to our knowledge, digital interventions including web-based delivery of sessions for ARFID are currently lacking.

Therefore, the aim of the present pilot intervention study will be to evaluate the feasibility and proof-of-concept of a CBT-AR based digital intervention “ExpeditionFood” for children and their parents/caregiver(s). Since sensory sensitivity is the most prevalent presentation of ARFID (4–6), the digital intervention will focus on individuals with sensory sensitivity. Based on the reported high prevalence in children ages 8–14 years (3, 4), the study will include children in this age range. Consequently, this study will simultaneously evaluate the feasibility of CBT-AR for a slightly younger age than in previous CBT AR trials (aged >10 years). Additionally, none of the previous cited interventions have been evaluated in German speaking countries where ARFID prevalence has been established (4, 20, 21). Hence, the primary aim of this study is to assess feasibility in German speaking countries and identify effect sizes for future randomized control trial. We hypothesize that a digital family supported intervention for children with ARFID will be feasible with acceptable recruitment and dropout rates and accepted by children and caregivers. Additionally, we hypothesize that the digital intervention will reduce ARFID symptoms, food neophobia and psychosocial impairment from pre- to post-intervention and will also increase quality of life. Finally, we will investigate if these effects are maintained until the four-week follow-up.

## Methods

2

### Design

2.1

We will conduct a single-arm clinical trial to evaluate the feasibility of a digital therapist-guided CBT-AR intervention for children with ARFID and their parents/guardians. The 12-week intervention will be based on the original manualized CBT-AR intervention translated to German. The CBT-AR specific food exposure strategies for sensory sensitivity will be delivered via a mixture of video therapy sessions and self-guided modules (14). Based on the reported high prevalence in children ages 8–14 years (3, 4), the study will focus on this age range. As CBT-AR has been developed from the age of 10 years on, we made a few adaptions to adopt for the slightly younger age range. Firstly, to decrease treatment burden on the children with often lower treatment motivation (23), we will offer self-guided sessions for parents/guardians and the child will join for the family supported video therapy sessions only. Secondly, we developed psychoeducational materials for the different ages with psychoeducational stories to enhance engagement of the younger children and different aged case examples. We will assess primary and secondary outcomes at pre-assessment/baseline, mid-assessment, post-assessment and 4-week follow up. Parents/guardians and children will be gifted a small coupon for completing the assessments. No incentive will be provided for participation in the intervention itself. Furthermore, the study is registered in the German Registry of Clinical Studies (Deutsches Register Klinischer Studien: DRKS00038026).

### Inclusion and exclusion criteria

2.2

Inclusion criteria include an age between 8 to 14 years with a primary diagnosis of ARFID and a primary presentation of sensory sensitivity as indicated by the ARFID module for the Eating Disorder Examination (ChEDE) (33). Children may have additional other phenotypes of ARFID or comorbidities. The ChEDE assesses all three presentations of ARFID and is currently the only available validated expert-interview in German. Exclusion criteria for the children include severe underweight (<3rd percentile); reliance on tube feeding; medical conditions prohibiting current treatment indicated by parents/guardians or pediatric doctor; changes in psychopharmacological treatment in the previous two months; comorbidities that would reduce the appropriateness of the intervention (e.g., psychotic disorder); acute suicidality; substance abuse; or concurrent psychotherapy, dietetic/nutritionist consultation or occupational therapy. In the case of concurrent treatment, patients can participate if they and their present health care provider prefer study participation and agree to pause any concurrent treatment. Lastly both the child and the caregiver have to be sufficient in German to understand the intervention content. Other than that, no additional exclusion criteria for caregivers apply.

### Recruitment and sample size

2.3

Recruitment will take place in Germany, Switzerland, Austria where German is (at least one of) the officially spoken languages. We will recruit families via the study’s website, social media (e.g., Instagram, Facebook), flyers, articles in our university press, and advertisements provided to outpatient health care providers affiliated with Konstanz University.

We conducted a power analysis with G*Power (version 3.1) to estimate a sample size, and also considered the sample sizes used in previous one-arm CBT-AR trials (10, 11, 15, 34). Hence, we based our power analysis on a = 0.05 and 1-b = 0.95, and a medium-sized effect size of f = 0.6, which resulted in a sample size of n = 32. To account for an expected dropout rate of 20-30% (15), we will aim to recruit *N* = 40. However, as the primary aim is to assess overall feasibility and acceptability and our main secondary aim is to identify effect sizes for randomized control trials, we are aware that depending on dropout rates the power might not be sufficient to make conclusions about the efficacy.

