### Proposed statistical analysis

2.10

As our primary aim is to assess feasibility, we will report recruitment rates and retention rates and number of adverse events until post-assessment with descriptive statistics. We will also report feasibility ratings of parents regarding the duration of sessions and materials, number of foods tasted per week, as well as the overall therapy duration of individuals completing the intervention. Acceptability will be descriptively reported based on parents rating on the treatment credibility (Credibility/Expectancy Questionnaire (CEQ) (48) and treatment satisfaction (Client Satisfaction Questionnaire (CSQ) (49)), as well as single-items for children.

As a secondary aim we will analyze ARFID symptoms reduction with paired sample t-test for expert-rated psychosocial impairment and sensory sensitivity (based on the Eating Disorder Examination (EDE) ARFID module, as well as self-report measures of symptoms of ARFID (i.e., Nine Item Avoidant/Restrictive Food Intake disorder screen (NIAS) (43) and Food Neophobic Scale (FNS) (44)) and children’s quality of life will be conducted from pre- to post assessments and pre-to follow-up.

Exploratory, in line with previous research we will also analyze anxiety (STAI (47)) and depression levels (Children’s Depression Screeners (46)) using dependent t-tests to test for potential changes in comorbid symptoms (12, 15).

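### The effect size behind n = 32 is on the wrong scale (f) for the planned paired t-test; 32 follows from dz = 0.6 with a one-sided test, and neither is stated

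*Protocol article*

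**What the plan says.** Section 2.3 (Recruitment and sample size) reports the tool, "We conducted a power analysis with G*Power (version 3.1) to estimate a sample size", then the error rates, "we based our power analysis on a = 0.05 and 1-b = 0.95", then the effect and the result, "a medium-sized effect size of f = 0.6, which resulted in a sample size of n = 32". It names no test, no outcome and no sidedness. It allows for 20–30% dropout and sets recruitment at 40. It then warns that, depending on dropout, power may be too low for conclusions about efficacy.

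Section 2.10 (Proposed statistical analysis) plans a "paired sample t-test for expert-rated psychosocial impairment and sensory sensitivity". The same test is applied to the NIAS, the Food Neophobia Scale and quality of life, comparing baseline with post-treatment and baseline with follow-up. No ANOVA is planned, and sidedness is again not given. Section 2.1 (Design) describes one arm: "We will conduct a single-arm clinical trial to evaluate the feasibility". The Introduction words its hypotheses directionally: "we hypothesize that the digital intervention will reduce ARFID symptoms, food neophobia and psychosocial impairment from pre- to post-intervention".

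**The concern.** The effect size of a paired t-test is dz, the mean change divided by the standard deviation of the changes. Cohen's f belongs to ANOVA and is a different quantity. A reader who enters the printed f, alpha and power for a one-group, two-occasion ANOVA does not obtain the printed n.

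Two things are at stake. First, the 95% power holds for the planned test only under a one-sided alternative that the article does not declare. If the t-tests are reported two-sided, as an unqualified paired t-test usually is, the trial has less power than it states. Second, Section 2.3 gives the main secondary aim as identifying effect sizes for later randomised trials, so a planning value on the wrong scale could mislead whoever plans those trials. Calling 0.6 medium adds to the confusion: the usual medium values are f = 0.25 and d = 0.5.

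**Working it through.** **Inputs.** Alpha 0.05, power 0.95, effect 0.6 and n = 32 come from Section 2.3. The paired t-test and its two-occasion comparisons come from Section 2.10, and the single arm from Section 2.1. Sidedness and the correlation between occasions are not given, so both are varied.

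**1. Reproducing 32 for the planned test.** Exact power comes from the noncentral t distribution with df = n − 1 and noncentrality dz × √n. Put dz = 0.6.

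| Pairs | Noncentrality | One-sided power | Two-sided power |
|---|---|---|---|
| 28 | 0.6 × √28 = 3.175 | 0.926 | 0.864 |
| 31 | 0.6 × √31 = 3.341 | 0.947 | 0.898 |
| 32 | 0.6 × √32 = 3.394 | **0.953** | **0.908** |
| 38 | 0.6 × √38 = 3.699 | 0.976 | 0.950 (0.9496) |
| 39 | 0.6 × √39 = 3.747 | 0.979 | **0.955** |
| 40 | 0.6 × √40 = 3.795 | 0.981 | 0.959 |

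The smallest n reaching 0.95 is 32 one-sided and 39 two-sided. The normal approximation agrees closely: ((1.645 + 1.645)/0.6)² = 30.1, so 31 one-sided; ((1.960 + 1.645)/0.6)² = 36.1, so 37 two-sided.

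**2. Reading f = 0.6 literally.** For one group measured m times with correlation ρ and sphericity, power comes from the noncentral F distribution with df m − 1 and (n − 1)(m − 1), and noncentrality λ = n × m × f²/(1 − ρ).

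- m = 2, ρ = 0.5: n = 12, λ = 12 × 2 × 0.36/0.5 = 17.28, power 0.965.
- m = 2, ρ = 0: n = 21, λ = 21 × 2 × 0.36 = 15.12, power 0.959.
- m = 3, 4, 5: n = 9, 8, 7 at ρ = 0.5, and 16, 14, 12 at ρ = 0.

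The range is 7 to 21. A two-group one-way ANOVA at f = 0.6 needs 40 in total, but there is only one arm.

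**3. Size of the gap if tests are two-sided.** At 32 completers the type II error is 1 − 0.908 = 0.092, against the stated 0.05. A two-sided test with 32 pairs reaches 95% power at dz = 0.66.

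**4. Completers from 40 recruited.** At 20% dropout, 40 × 0.8 = 32. At 30%, 40 × 0.7 = 28. The rows for 28 and 32 in the table therefore span the plan's own dropout range.

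**The case against.** The strongest reply is that 32 is very probably right for the test that was meant. It matches a one-sided paired t-test at dz = 0.6 exactly, the hypotheses are directional, and a one-sided test is legitimate. On that reading the sample size is sound and only a symbol and an option are misreported. Sidedness is also a detail that a condensed article may leave to a fuller document. The part that stands: the number can be recovered, the plan does not commit to two-sided tests, and any shortfall is conditional on them. The part that does not: the printed effect size is on the wrong scale for the planned test, and no later document can make f = 0.6 yield 32 for a paired t-test.

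Nor is 32 unreachable by any other route. A one-sided Wilcoxon signed-rank test gives 33. Some ANOVA settings with f = 0.6 land at 30 to 32, for example an alternative (SPSS-type) definition of f with a nonsphericity correction, or a three-group between-subjects factor. None of these is the planned paired t-test in one arm, and the article mentions none of them.

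The consequence is limited too. The primary aim is feasibility, reported descriptively against benchmarks in Section 2.8.1 that do not use this calculation. Section 2.3 already warns about power. That warning concerns dropout, whereas the two-sided gap exists with all 32 completing, so it softens the point without removing it.

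**Conclusion.** The concern holds as a correction to the stated power, at should-fix level. The printed inputs do not yield 32 for the planned analysis. The figure follows once f is read as dz and the test is taken as one-sided. If the tests are two-sided, power at dz = 0.6 is 0.91 rather than 0.95 with 32 completers, and 0.86 with 28. These figures assume approximately normal changes; the ANOVA figures also assume sphericity.

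A reader might infer that the sample size is wrong and must rise to 39 completers, which would mean recruiting 39/0.8 = 49 (rounded up) at 20% dropout. The documents do not support that, because they nowhere commit to two-sided testing and their directional hypotheses make an undeclared one-sided test plausible. A reader might also infer that the trial is powered for dz = 0.5 because the effect is called medium. The planning value is 0.6, and the label is merely loose.

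**What to change.** In Section 2.3, replace the description of the effect as a medium-sized f with *standardised paired change dz = 0.6*, drop the word medium, and name the paired t-test and the outcome that the calculation refers to. Then take one of two routes:

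- **One-sided tests intended:** declare one-sided alpha 0.05 in both Section 2.3 and Section 2.10. The 0.95 then stands at 32 completers, and 0.93 can be quoted for 28.
- **Two-sided tests intended:** say so in both sections and restate the power as 0.91 at 32 completers, with 0.96 at 40 and 0.86 at 28.

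The cost is a few words and, on the second route, a slightly less favourable power figure. The recruitment target of 40 and the primary analysis do not change.

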#### Feasibility and acceptability

2.8.1

We will assess feasibility via a retention rate. Rates ≥ 70% from pre- to post-assessment will be considered successful (39, 40). Another indicator will be the number of adverse events reported by the parents or child. Parents/guardians will be asked to report potential adverse events at the end of each session based on the recommendation for internet-intervention (41). Based on previous feasibility studies in children with ARFID we will consider a recruitment rate of ≥1 patient per month as feasible (11, 15). Additionally, based on similar research studies we will apply the following benchmarks enrolment (≥75% eligible participants enrol in the intervention). As an indicator of participants engagement, we will assess the number of times patients tasted new foods over the course of the intervention and how many different foods they tasted per week. Furthermore, we will report the average time needed to complete the intervention.

Additionally, we will ask parents and children at mid- and post treatment to rate the perceived feasibility of different intervention parts (e.g., weekly psychoeducational materials, video therapy sessions). These include ratings on the feasibility of time and effort needed for the intervention, understanding of the materials and satiation with technical quality of the platform on a 6-Point Likert scale (0 = completely agree to 1 = completely disagree). We will also measure parents’ acceptability of the intervention will by the Credibility/Expectancy Questionnaire (CEQ) (42) completed by parents and a single-item for the children.

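### N = 40 covers only the 20% end of the stated 20–30% dropout; at 30% it leaves 28 pairs rather than the required 32 (minor, wrong as written)

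*Protocol article*

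**What the plan says.** Section 2.3 (Recruitment and sample size) of the protocol article reports a G*Power calculation with "a = 0.05 and 1-b = 0.95" and "a medium-sized effect size of f = 0.6, which resulted in a sample size of n = 32". It adds that the sizes of previous trials were also considered. It then sets the recruitment target: "To account for an expected dropout rate of 20-30% (15), we will aim to recruit" N = 40. The closing sentence of the section makes feasibility and acceptability the primary aim and effect sizes for later randomised trials the main secondary aim. It concedes that "depending on dropout rates the power might not be sufficient to make conclusions about the efficacy".

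Section 2.10 names the analysis that the calculation serves: "we will analyze ARFID symptoms reduction with paired sample t-test for expert-rated psychosocial impairment and sensory sensitivity". The same test is planned for the self-report symptom measures and quality of life, from pre to post and from pre to follow-up. Whether the tests are one- or two-sided is not stated. The hypothesis in the Introduction is directional: "we hypothesize that the digital intervention will reduce ARFID symptoms, food neophobia and psychosocial impairment from pre- to post-intervention".

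**The concern.** A paired t-test uses only participants measured at both times, so the 32 from the power calculation must be 32 completed pairs. A recruitment target said to account for a dropout range should still deliver that number at the upper end of the range. N = 40 delivers it only at the lower end.

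What is at stake is the accuracy of a stated design figure. A reader would take from section 2.3 that the calculated size is protected up to 30% dropout and that any shortfall begins beyond that. In fact it begins as soon as dropout exceeds 20%. Because the trial is meant to inform the planning of later randomised trials, its own sample-size reasoning should be arithmetically consistent.

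**Working it through.** **Inputs.** From section 2.3: alpha 0.05, power 0.95, effect size 0.6, required n = 32, dropout 20–30%, target N = 40. From section 2.10: paired t-test. Two inputs are assumed because the article does not settle them: that 0.6 (written as f) is the standardised paired change, that is, mean change divided by the SD of the changes; and that the test is one-sided.

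**Step 1: reproduce n = 32.** Power of a one-sided paired t-test is the probability that a noncentral t variable with n − 1 degrees of freedom and noncentrality 0.6 × √n exceeds the 95th percentile of the central t distribution.

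- n = 31: power 0.947, below target.
- n = 32: noncentrality 0.6 × √32 = 3.39, power 0.953. This is the smallest n that reaches 0.95 and matches the article.
- A two-sided test needs n = 39.
- Reading 0.6 as Cohen's f does not give 32. Repeated-measures ANOVA, with an assumed correlation of 0.5, gives 12, 9 and 8 for 2, 3 and 4 time points; between-group ANOVA gives 39 or more.

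The one-sided paired test with a standardised change of 0.6 is therefore the reading used below.

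**Step 2: recruits needed to keep 32 pairs**, n / (1 − dropout):

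- 20%: 32 / 0.80 = 40
- 25%: 32 / 0.75 = 42.7, so 43
- 30%: 32 / 0.70 = 45.7, so 46

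The target of 40 equals the first line exactly. It also equals 32 × 1.25, which is what adding the mid-range 25% to 32 would give. The article does not show its step, so which route was taken cannot be told.

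**Step 3: pairs left from N = 40, and the power they give** (standardised change 0.6, alpha 0.05):

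| Dropout | Pairs left | Power, one-sided | Power, two-sided |
|---|---|---|---|
| 20% | 40 × 0.80 = 32 | 0.953 | 0.908 |
| 25% | 40 × 0.75 = 30 | 0.941 | 0.888 |
| 30% | 40 × 0.70 = 28 | 0.926 | 0.864 |

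**Step 4: the part due to dropout.** Going from 32 to 28 pairs costs 0.953 − 0.926 = 0.027 one-sided and 0.908 − 0.864 = 0.044 two-sided. In the two-sided column, the gap between 0.95 and 0.908 is already present at 32 pairs and has nothing to do with dropout. For estimating effect sizes, 28 instead of 32 pairs widens a confidence interval by a factor of about √(32/28) = 1.07.

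**The case against.** The strongest reply is that section 2.3 already discloses the limitation. Its last sentence names dropout as the cause and insufficient power as the consequence. The article never states outright that power is 95% at 30% dropout, and it does not rest the sample size on the power calculation alone. Efficacy testing is secondary, and 93% power is high for a pilot. All of this stands, and it is why the point is minor. What it does not do is correct the sentence before it: the caveat gives no number of pairs and no power, and does not say that the shortfall begins inside the expected range.

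Three stronger readings are tempting, and the documents do not support them.

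- A reader might set 0.86 against the stated 0.95 and attribute the whole gap to dropout. That mixes in the unstated sidedness: a two-sided test has only 0.91 with all 32 pairs.
- A reader might see a contradiction with section 2.8.1, where "Rates ≥ 70% from pre- to post-assessment will be considered successful", since 70% of 40 is 28. That mark is a feasibility benchmark reported descriptively, not a power criterion. A trial can be feasible at 70% retention while its secondary tests have 28 pairs, so this adds no separate error.
- A reader might conclude that the 4-week follow-up comparisons will certainly have fewer pairs. No attrition figure for follow-up is given, so they may have fewer, and no more can be said.

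**Conclusion.** The statement that N = 40 accounts for 20–30% dropout is wrong as written. It holds at 20% and at no higher rate within the range: the shortfall against the required 32 is 2 pairs at 25% and 4 pairs at 30%. This part rests only on figures in section 2.3.

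The consequence is small: power of 0.95, 0.94 and 0.93 at 20%, 25% and 30% dropout. These values assume a one-sided paired t-test at alpha 0.05 with 0.6 as the standardised paired change, and that dropout removes pairs one for one. The primary feasibility outcomes do not depend on them. This is a minor correction to the sample-size statement; it does not show that the trial is too small for its purpose.

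**What to change.** Keep N = 40 and replace the dropout sentence in section 2.3 with wording such as:

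> N = 40 gives 32 pairs at 20% dropout and 28 at 30%; power for a standardised paired change of 0.6 (one-sided alpha 0.05) is 0.95 and 0.93.

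Remove the claim that N = 40 covers 30% dropout. If the tests are to be two-sided, report 0.91 and 0.86 instead, and note that the shortfall at 32 pairs comes from the sidedness of the test and not from dropout. One clause may add that follow-up comparisons may have fewer pairs.

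The cost is one sentence and a slightly less favourable power figure, with no additional families. The alternative of protecting 32 pairs across the whole range would mean recruiting 46, which a gain of under 3 percentage points of power on secondary outcomes hardly justifies in a feasibility trial.
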